#### Interim analyses {21b}

There are no planned interim analyses for efficacy or futility but an independent Data Monitoring Committee (DMC) will monitor trial progress and any safety issues.

#### Methods for additional analyses (e.g. subgroup analyses) {20b}

The following subgroup analyses are planned:Women vs menNeuropathic bladder vs. non-neuropathic bladderAge groups: < 45 vs. 45–64yrs vs. > 65Participants with no history of LTC blockages versus those with recurrent blockagesParticipants with no history of S-CAUTI vs those with recurrent S-CAUTIParticipants with baseline urinary pH: normal range vs alkaline vs acidic

All subgroup analyses will be at the 99% significance level.

An economic evaluation is integrated into the trial and includes both a trial-based analysis and a modelling exercise to extrapolate the results over the patient’s lifetime. Outcomes and costs are assessed from the perspective of the NHS and patients. Effectiveness is measured in terms of quality-adjusted life years gained.

Qualitative interview and focus group transcripts will be analysed using an explicit, structured qualitative method of thematic analysis.

#### Methods in analysis to handle protocol non-adherence and any statistical methods to handle missing data {20c}

Data missing at baseline will be reported as such. If required, missing baseline primary and/or secondary outcome data will be imputed with centre specific mean for continuous data and missing binary/categorical data will include a missing indicator. Multiple imputation methods will be used for missing outcome data.

#### Plans to give access to the full protocol, participant-level data and statistical code {31c}

The full protocol is available on the NIHR website under award listing 17/30/02. Requests for participant-level data and/or statistical code can be made in writing to [name].

### Oversight and monitoring

#### Composition of the coordinating centre and trial steering committee {5d}

The trial office provides day-to-day support for the study sites and meets formally at least monthly. The trial manager takes responsibility for the day-to-day transaction of trial activities. The data coordinator provides clerical support to the trial.

The trial is supervised by its Project Management Group (PMG) which consists of the grant holders and representatives from the trial office, including the trial manager, data coordinator, statistician, health economist and qualitative researcher. The PMG meet at least quarterly throughout the study.

A Trial Steering Committee (TSC), with independent members, oversees the conduct and progress of the trial. The TSC meet at least annually throughout the study.

#### Composition of the data monitoring committee, its role and reporting structure {21a}

An independent Data Monitoring Committee (DMC) oversees the safety of subjects in the trial. The DMC comprises members with clinical, statistical and methodological expertise. The charter is filed in the TMF. The Committee meet at least annually throughout the study to monitor the trial data and make recommendations to the TSC.

#### Adverse event reporting and harms {22}

In CATHETER II, serious adverse events (SAEs) are recorded from each participant from the time a participant consents to joining the study until their last trial follow-up. The occurrence of SAEs is queried by the site at every contact with the participant or the person carrying out the washout. An event must be serious and related to the catheter or the catheter washout procedure to be considered an SAE in CATHETER II. In addition, all deaths by any cause are recorded as SAEs in CATHETER II. Adverse events captured as outcome measures (for example, catheter blockage) for the study are not reported through SAE processes. Any hospitalisation or prolongation of hospitalisation planned prior to randomisation, for elective treatment of a pre-existing condition or due to events captured as outcome measures are not recorded as SAEs. The investigator (or delegate) reviews appropriate documentation related to the SAE and records the details on the SAE form. If an SAE is recorded on a participant questionnaire, the trial office liaises with the clinical team to obtain further information if appropriate. The seriousness, relatedness and expectedness of the event are evaluated by the Investigator or the CI or delegate. If an event is confirmed as being a related and unexpected SAE, the trial office notifies the sponsor within 24 h and the CI (or delegate) reports any related and unexpected SAEs to the Research Ethics Committee (REC) within 15 days of the CI being aware of the event. All SAEs are regularly reported in progress reports to the REC, funder, DMC and TSC.

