LTC can be associated with several adverse events [5] which affect the daily life of patients and can consume substantial NHS resources [8]. Wilde et al. reported typical adverse events of LTC blockage (34% of participants): symptomatic catheter-associated urinary tract infections (S-CAUTI), whether or not this has been proven bacteriologically (57%); accidental dislodgment (28%); urinary leakage (67%); bladder spasms (59%); kinks/twists (42%) and pain (49%) [1].

LTC blockages often occur secondary to the formation of encrustations on the luminal and outer surfaces of the catheter, with an incidence of 40–50% in patients in most studies [7, 9–11]. Wilde et al. in 2017 [1] assessed 202 patients with LTC over 12 months and showed that 34% of patients reported blockage and a rate of 8.54/1000 days of catheter use. Catheter blockage is considered a medical emergency and can lead to distress, autonomic dysreflexia in patients with spinal cord injury at or above T6, increased healthcare utilisation and urosepsis [12]. Current best practice for the management of LTC blockage requires a regular (and more frequent) change of the catheter [3]. Catheter washouts are often used in these cases despite the lack of evidence on their benefit, potential harm, best solution to be used, appropriate volume and frequency, and individual impact on quality of life among patients with LTC [2].

Several catheter washouts policies are used in clinical practice for the prevention and/or management of LTC blockage. Washouts used are of different types (normal saline, acidic, antimicrobial), volumes and frequency of administration. The Cochrane review [2] assessed the best available evidence and concluded that there is insufficient evidence to determine whether prophylactic catheter washout policies had a beneficial or harmful effect on any of the outcomes in patients with LTC. The authors recommended a rigorous and methodologically robust randomised controlled trial to assess the clinical and cost-effectiveness of washout policies in patients with LTC.

Muncie et al. [13] compared saline washouts versus no washouts policy over 24 weeks in a limited population and showed no significant differences in S-CAUTI per 100 days of catheter use. Concerns exist that the use of washouts can damage the bladder mucosa and possibly increase the risk of S-CAUTI. NICE CG139 recommend that “[catheter] washouts must not be used to prevent catheter-associated infections” [3].

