### Trial design {8}

CATHETER II is a pragmatic three-arm, parallel-group, open multi-centre superiority randomised controlled trial. It compares the clinical and cost-effectiveness, patient acceptability and satisfaction, and safety of weekly prophylactic catheter washouts policies in addition to standard long-term catheter (LTC) care compared to standard LTC care only, in adults living with LTC.

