#### Intervention description {11a}

The interventions being compared are:*Intervention arm (A):* Saline washouts. A policy of weekly prophylactic normal saline catheter washouts plus standard LTC care. One application of 100 ml 0.9% NaCl per washout (Uro-Tainer® NaCl 0.9% CE)*Intervention arm (B):* Acidic washouts. A policy of weekly prophylactic acidic catheter washouts plus standard LTC care. Two sequential applications of 30 ml 3.23% citric acid per washout (Uro-Tainer® Twin SUBY G)*Control arm (C):* Standard LTC care only with no prophylactic catheter washout

Washouts are administered in accordance with best practice technique at the time of the regular weekly catheter bag or valve change, to reduce the risk of introducing infection by minimising the breakage of the closed drainage system. Participants and/or their relatives, friends, or other informal carers will receive training to administer catheter washouts from an appropriately trained member of the local study team to enable them to self-administer the washouts in accordance with best practice. Training is provided with either face-to-face or by video/phone consultation and is supported with an online training video and hardcopy instructions for use with troubleshooting advice. If a health professional usually changes the catheter bag or valve for a participant and capacity and capability allows, they will be asked to undertake training and perform the washout within the study. The washouts are couriered directly to the participant from the trial office.

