### Assignment of interventions: blinding

#### Who will be blinded {17a}

It is not possible to blind the allocated study arm.

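### Non-fatal serious events become SAEs only after an unblinded relatedness judgement that names the washout procedure, which risks unequal SAE ascertainment between arms

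*Protocol article*

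**What the plan says.** Under Adverse event reporting and harms {22}, the protocol article makes relatedness a condition of entry: "An event must be serious and related to the catheter or the catheter washout procedure to be considered an SAE in CATHETER II". There is one exception: "In addition, all deaths by any cause are recorded as SAEs in CATHETER II". The judgement is assigned as follows: "The seriousness, relatedness and expectedness of the event are evaluated by the Investigator or the CI or delegate". The article mentions no masked or independent adjudication, and Who will be blinded {17a} says: "It is not possible to blind the allocated study arm".

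The same harms section keeps events that are already outcome measures, and hospital stays caused by them, out of the SAE process.

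Intervention description {11a} defines arm C as "Standard LTC care only with no prophylactic catheter washout". Trial design {8} lists among the comparisons the "safety of weekly prophylactic catheter washouts policies in addition to standard long-term catheter (LTC) care compared to standard LTC care only".

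Outcomes {12} includes adverse events, S-CAUTI treated with antibiotics, and hospital admissions, the last restricted to catheter-related complications. Table 1 shows blockage, S-CAUTI, catheter change, adverse events and NHS/healthcare use collected monthly for 24 months, with no distinction by arm.

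**The concern.** Relatedness here is not a label attached to an event that has already been recorded. It decides whether a non-fatal serious event becomes an SAE at all. The person deciding can know the allocation, and one of the two qualifying routes is the washout procedure, to which control participants are not exposed by allocation. The same clinical event could be called related in arm A or B and unrelated in arm C, or the reverse if the person deciding regards washouts as routine and benign.

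At stake is the comparison of non-fatal SAEs between each washout policy and standard care. A difference could appear with no true difference in serious events, or a true difference could be hidden. An event judged unrelated leaves no SAE record, so the SAE data alone cannot show whether attribution differed by arm. SAE reports also go to the DMC, the TSC, the funder and the REC.

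**Working it through.** **Step 1: what passes through the gate.** The sections, set side by side:

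| Event type | Relatedness judgement needed? | Source |
|---|---|---|
| Non-fatal serious event, not an outcome measure | Yes, to catheter or washout | {22} |
| Death, any cause | No | {22} |
| Blockage, S-CAUTI, monthly adverse events | Not subject to the SAE gate | {12}, {18a}, Table 1 |
| Hospital admission as a secondary outcome | Limited to catheter-related complications | {12} |
| Hospital stay due to an outcome event | Outside the SAE process | {22} |

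The gate therefore bears on non-fatal SAEs. The one outcome that could check them, hospital admissions, carries a similar attribution step.

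**Step 2: who has which route.** The catheter route exists in all three arms. The washout route exists by allocation in A and B. It can also open in arm C, because {11b} lets control participants start prophylactic washouts after review, and {12} counts a washout as an intervention for blockage without naming an arm.

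**Step 3: illustration of size.** The article gives no SAE rate and no share judged related, so there is no stated figure to reproduce. The only input taken from it is 200 participants per arm. Assumed: the same true number T of non-fatal serious events in each arm over 2 years, Poisson counts, a share qC = 0.30 judged related in control and qT in one washout arm.

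- Expected recorded SAEs: Ec = T × qC and Et = T × qT.
- Recorded rate ratio: Et/Ec = qT/qC, because T cancels.
- SE of the log ratio = √(1/Ec + 1/Et).
- Chance of a nominally significant result when the true ratio is 1 = Φ(d − z) + Φ(−d − z), where d = ln(qT/qC)/SE.

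Worked case, T = 100 and qT = 0.40: Ec = 30, Et = 40, ratio 1.33; SE = √(1/30 + 1/40) = 0.2415; d = 0.2877/0.2415 = 1.19. With z = 1.96 the chance is 0.22.

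One washout arm against control, 200 vs 200:

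| qT | Ratio | T = 60 to 100, two-sided 5% | T = 60 to 100, two-sided 2.5% | T = 10 to 20, two-sided 2.5% |
|---|---|---|---|---|
| 0.30 | 1.00 | 5% | 2.5% | 2.5% |
| 0.35 | 1.17 | 8–10% | 4–5% | 3% |
| 0.40 | 1.33 | 15–22% | 9–15% | 4–5% |
| 0.45 | 1.50 | 27–41% | 18–30% | 5–7% |

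The 2.5% level is the one in Sample size {14}, taken here as two-sided. The last column allows for few events reaching the gate once outcome events are removed; with about 3 to 9 expected recorded events per arm the normal approximation is rough.

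**Step 4: direction.** The ratio depends only on qT/qC. With qC = 0.40 and qT = 0.30 it is 0.75, and a true ratio of 1.33 would then be recorded as 1.33 × 0.75 = 1.00. Nothing in the article settles which way the shares would differ.

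**The case against.** The strongest reply is that most safety information does not pass through this gate. Deaths are recorded whatever the cause, and blockage, S-CAUTI, adverse events and healthcare use are collected monthly in every arm. That stands. A reader might infer that the whole safety comparison is filtered unequally; the document does not support this.

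A reader might also infer that only treated participants can qualify through the washout. Sections {11b} and {12} show otherwise. Moreover, naming the procedure has a proper purpose, since harm caused by a washout is what a safety comparison should capture. The weakness is the unblinded condition of entry, not the mention of washouts.

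A third tempting reading is that SAEs will be inflated in the washout arms, because the background section says: "Concerns exist that the use of washouts can damage the bladder mucosa and possibly increase the risk of S-CAUTI". But S-CAUTI is an outcome measure, so it and admissions due to it stay outside the SAE process. The article does not say that site staff are told of this concern, and it describes washouts as common practice. The direction is open.

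Finally, the sentence "The occurrence of SAEs is queried by the site at every contact with the participant or the person carrying out the washout" may suggest an informant that arm C lacks. Eligibility {10} requires every participant to be able to do washouts or to have someone who can, consent for that person is provided for in {26a}, and monthly collection in {18a} is from the participant or carer in any arm. No change of informant is needed.

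The full protocol is not shown and may give guidance on attribution or on recording other adverse events. That limits what can be said about events judged unrelated: they leave no SAE record, but it cannot be shown that they leave no record anywhere. It does not alter the rule that the article states.

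**Conclusion.** The point holds for non-fatal SAEs. Their recording as SAEs depends on an unblinded relatedness judgement with one route tied mainly to arms A and B, while safety against standard care is a stated aim. This creates a risk of differential ascertainment; it does not demonstrate a bias. The catheter-related admissions outcome does not remove the risk, because it needs the same kind of judgement.

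Size and direction rest wholly on assumption. On the shares used above, the recorded ratio for one washout arm against control is 1.17 to 1.50 with no true difference, and it falls below 1 if attribution leans the other way. The chance of a false signal runs from barely above nominal, with few eligible events, to 41% in the most extreme case shown. The article states no formal test of SAEs, so these chances only gauge how misleading a comparison could be. The primary outcome is not affected. The change is worth making because it is cheap and a stated aim depends on it.

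**What to change.** Keep the relatedness rule for SAE forms and expedited reporting. Add to the planned safety analysis a comparison, for each washout arm against control, of (a) all unplanned hospital admissions from any cause, including those due to outcome events, and (b) all deaths, both regardless of judged relatedness. Collect the admissions in every arm at the existing monthly contact through the NHS/healthcare-use item, and word that item so that it is not restricted to catheter-related admissions. Judged relatedness can still be tabulated as a description.

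The cost is one extra CRF line and one sentence in the analysis plan, with no added visits or expedited reports. The drawback is that many of the added events will have nothing to do with the catheter, which adds noise to the safety table and can dilute a true washout effect. For that reason the comparison should stand beside the related-SAE listing and not replace it.

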#### Frequency and plans for auditing trial conduct {23}

The trial office monitors oversight arrangements, training, set-up, data collection and safety as detailed in the study monitoring plan. The sponsor audits and monitors the trial and individual sites may have further arrangements locally for monitoring.

#### Plans for communicating important protocol amendments to relevant parties (e.g. trial participants, ethical committees) {25}

Protocol amendments require approval by the sponsors, funder, REC and the site. B. Braun Medical AG is notified of protocol amendments.

#### Dissemination plans {31a}

Trial results will be published in journals and presented at conferences and shared with relevant patient and clinical interest groups. A lay summary of the findings will be sent to participants.

## Discussion

Catheter care pathways are complex and heterogenous across the UK, with varying involvement and responsibilities for prescriptions, catheter changes and clinical management across GP practices, district and community nurses, secondary/tertiary care and social care. The CATHETER II study adopts multiple recruitment strategies to identify and recruit potentially eligible participants.

Recruitment to the study was temporarily paused at the onset of the COVID-19 pandemic. Adaptations made to the study protocol to limit face-to-face contact, minimise the risk to participants and research staff and resume recruitment included: the use of post and telephone for consent and baseline data collection; the training of participants and/or their carer to administer washouts by video consultation (where possible); the adoption of local/NHS infection control policy where face to face training to administer washouts is required; optional baseline urine dipstick pH test with participants provided with testing kits and instructions to self-perform the test; and pre-recorded webinars replacing site initiation visits. Follow-up proceeds by post and telephone as per the original protocol. At the time of submission of this publication, the study continues to be delivered in accordance with these COVID-19 pandemic adaptations.

A 2019 qualitative study [22] cited potential recruitment barriers in a hypothetical clinical trial comparing regular catheter washouts against standard care. One barrier is patients being unwilling to change their current catheter care if they are happy with how it is currently managed. The CATHETER II protocol permits changes to washout policy if clinically necessary. Another cited recruitment barrier is the complex health issues/co-morbidities in the study population with these patients often not having time to commit to research. CATHETER II minimises face-to-face clinical visits, with nearly all study activities delivered remotely by post, phone and videocall. Feedback from sites to date indicates that these barriers remain an issue for a proportion of potential participants.

No other robust randomised controlled trials investigating the study question are published or in progress. The research question remains a very important clinical dilemma for patients, clinicians, nursing organisations and NHS policymakers.

## Trial status

Recruitment commenced on 12 December 2019. Recruitment to the trial was paused on 16 March 2020 due to the COVID-19 pandemic and re-opened to recruitment in September 2020. Due to ongoing delays as a result of the COVID-19 pandemic, it is not possible to provide an approximate end date for the recruitment. The current protocol is version 10, 07 March 2022.

## Data Availability

The trial statistician and health economist will have access to the full dataset to permit analysis at the end of the trial. The final trial dataset generated and/or analysed during the current study may be available on reasonable request to the CI.

## Abbreviations

CRF: Case report form
DMC: Data Monitoring Committee
EQ-5D-5L: EuroQol Questionnaire – 5 Dimensions – 5 Levels
GCP: Good Clinical Practice
GP: General practitioner, general practice
GSE: General Self-Efficacy Scale
ICECAP-A: ICEpop CAPability measure for Adults
ICECAP-O: ICEpop CAPability measure for Older people
ICIQ-LTCqol: International Consultation on Incontinence Modular Questionnaire – Long-Term Catheter quality of life
LTC: Long-term catheter
NICE: National Institute for Health and Clinical Excellence
NIHR HTA: National Institute of Health Research Health Technology Assessment Programme
NRS: NHS Research Scotland
PMG: Project Monitoring Group
REC: Research Ethics Committee
SAE: Serious adverse event
S-CAUTI: Symptomatic catheter-associated urinary tract infection
TSC: Trial Steering Committee
UK: United Kingdom
